#### Anatomical success

The calculation is based on the hypothesis that MOCA using Flebogrif will have no inferior anatomical success 12 months after treatment, compared with EVLA. The anatomical success rate in the EVLA group is expected to be 95%.^22^,^25^ The anatomical success rate in the Flebogrif group is expected to be 93%.^18^,^20^ A non-inferiority margin of −10% is applied. This margin is based on the anatomical success rate of 85% after MOCA using Clarivein.^14 25 26^ Taking into account a power of 80% and a significance level of 2.5% (one-sided test on the lower level of the 95% CI of the expected difference), 278 patients will be needed (https://www.sealedenvelope.com/power/binary-noninferior/). Corrected for 10% lost to follow-up, 155 patients need to be included in each treatment group. The total study population will consist of 310 patients.

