#### Withdrawal

Patients can leave the study at any time for any reason if they wish to do so without any consequences. The coordinating investigator can decide to withdraw a patient from the study for urgent medical reasons. After withdrawal, individual patients will not be replaced. If a patient is withdrawn from the study, follow-up ends.

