### Primary outcome

#### Anatomical success (at 12 months)

Anatomical success (at 12 months) is objectified at 12 months follow-up using DUS. DUS is performed with the patient in the upright position, applying manual compression to the calf and using the Valsalva manoeuvre to detect flow and reflux. Occlusion is defined as a non-compressible vein (segment) that subsequently lacks flow and reflux. Recanalisation is defined as a compressible vein (segment) with flow or reflux.

Anatomical success outcomes (at 12 months) are defined as:

Anatomical success: complete occlusion of the treated vein segment or a recanalised segment of ≤5 cm.Anatomical failure:Partial recanalisation: a recanalised segment of >5 cm.Complete recanalisation: recanalisation of the entire treated vein segment.

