#### Anatomical success (during other follow-up moments)

Anatomical success (during other follow-up moments) is objectified at 1 week, 1, 6, 24 and 60 month(s) follow-up using DUS. DUS is performed with the patient in the upright position, applying manual compression to the calf and using the Valsalva manoeuvre to detect flow and reflux. Occlusion is defined as a non-compressible vein (segment) that subsequently lacks flow and reflux. Recanalisation is defined as a compressible vein (segment) with flow or reflux.

Anatomical success outcomes (during other follow-up moments) are defined as:

Anatomical success: complete occlusion of the treated vein segment or a recanalised segment of ≤5 cmAnatomical failure:Partial recanalisation: a recanalised segment of >5 cm.Complete recanalisation: recanalisation of the entire treated vein segment.

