### Data analysis plan

The intention-to-treat (ITT) population will include all patients randomised to one of the two treatment groups. These groups will be analysed according to the ITT principle (analysed as randomised). The per-protocol (PP) population will only include those patients who underwent the procedure they were randomised to. Statistical analysis will be performed by using SPSS (IBM SPSS Statistics V.25).

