#### Primary outcome analysis

Anatomical success at 12 months of follow-up is a dichotomous variable and will be described as numbers with percentages. The difference between the two groups will be presented as a percentage with a 95% CI. If the lower limit of this CI does not exceed the non-inferiority margin of −10%, the intervention will be considered to be non-inferior. A second analysis will be performed in which data from the last follow-up visit before a reintervention will be used in patients undergoing a reintervention of the GSV after failure of primary treatment.

These analyses will be performed for both the ITT and the PP population. Patients with missing data on the primary outcome parameters will be excluded from analyses.

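### The ITT primary analysis is a complete-case analysis: an early failure with no recorded reintervention and no 12-month scan is lost from both planned primary analyses, and no other handling of missing outcomes is stated

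*Protocol article*

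**What the plan says.** Under Data analysis plan, the protocol article states: "The intention-to-treat (ITT) population will include all patients randomised to one of the two treatment groups". Under Primary outcome analysis, it applies the comparison with the −10% margin to both populations ("These analyses will be performed for both the ITT and the PP population") and then adds: "Patients with missing data on the primary outcome parameters will be excluded from analyses".

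The outcome that must be present is the 12-month duplex result: "Anatomical success (at 12 months) is objectified at 12 months follow-up using DUS". Duplex with the same success and failure definitions is also done earlier: "Anatomical success (during other follow-up moments) is objectified at 1 week, 1, 6, 24 and 60 month(s) follow-up using DUS". Under Withdrawal: "If a patient is withdrawn from the study, follow-up ends".

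One further analysis of the primary outcome is planned: "A second analysis will be performed in which data from the last follow-up visit before a reintervention will be used in patients undergoing a reintervention". It concerns only reinterventions of the GSV after failure of the primary treatment.

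The sample size section allows for loss: "Corrected for 10% lost to follow-up, 155 patients need to be included in each treatment group".

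**The concern.** The two statements on the ITT population do not fit together. One includes everyone randomised; the other removes everyone without the 12-month outcome. A patient with more than 5 cm of recanalisation at 6 months who then leaves the study has a recorded anatomical failure, yet drops out of both numerator and denominator.

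The second analysis narrows the gap without closing it. It can bring back an early failure that had a recorded GSV reintervention. It does not reach an early failure with no recorded reintervention, which would include one re-treated elsewhere without the site's knowledge.

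In a non-inferiority trial the direction of error matters. If failures are lost more often than successes, even at the same rates in both arms, the arm with more failures loses more of them. The observed difference shrinks and a false claim of non-inferiority becomes more likely. If failures are lost less often, the rule is conservative. The article gives no reason to expect either pattern, or loss unrelated to outcome.

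**Working it through.** **Inputs.** From the sample size section: EVLA success 95%, Flebogrif success 93%, margin 10 points, one-sided 2.5%, power 80%, 10% loss, 155 per arm. The article gives no missingness rates by outcome; all such rates below are assumptions.

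**1. The plan's own figure.** n per arm = (0.95×0.05 + 0.93×0.07) × (1.960 + 0.842)² / (0.10 − 0.02)² = 0.1126 × 7.849 / 0.0064 = 138.1. This rounds up to 139, or 278 in total. 139 / 0.90 = 154.4, rounded up to 155, or 310 in total. Both stated figures reproduce.

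**2. Missing patients against failures.** Expected missing per arm: 155 − 139 = 16. Expected failures among 139: EVLA 0.05 × 139 ≈ 7; Flebogrif 0.07 × 139 ≈ 10. More patients are expected to be missing than to fail.

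**3. False non-inferiority at the margin.** Truth is set at 85% (Flebogrif) vs 95% (EVLA), with 155 per arm. A proportion mf of failures and ms of successes is missing, the same in both arms. Observed success is p(1 − ms) / [p(1 − ms) + (1 − p)(1 − mf)].

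Example with mf = 0.30, ms = 0.08:
- Flebogrif: 0.782 / (0.782 + 0.105) = 88.2%, with 11.3% missing overall.
- EVLA: 0.874 / (0.874 + 0.035) = 96.2%, with 9.1% missing overall.
- Observed difference: −8.0 points instead of −10.

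The simulated chance that the lower Wald 95% limit lies above −10 is:

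| Failures missing | Successes missing | Observed difference | False non-inferiority |
|---|---|---|---|
| 0% | 0% | −10.0 | 3.0% |
| 10% | 10% | −10.0 | 3.1% |
| 15% | 10% | −9.5 | 4.2% |
| 20% | 10% | −9.1 | 5.7% |
| 30% | 8% | −8.0 | 11.2% |
| 5% | 10% | −10.4 | 2.3% |
| 0% | 11% | −11.0 | 1.6% |

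The baseline for comparison is about 3%, not the nominal 2.5%, because the Wald limit itself is slightly liberal here.

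**4. What would reverse the planned result.** The lower limit is d − 1.96 × √[p₁(1 − p₁)/n₁ + p₂(1 − p₂)/n₂].
- Complete case, 129/139 vs 132/139: d = −2.2, limit −7.8, non-inferior.
- Add back 16 per arm, with 4 Flebogrif failures and 1 EVLA failure, 141/155 vs 147/155: d = −3.9, limit −9.6.
- The same with 5 Flebogrif failures and 1 EVLA failure, 140/155 vs 147/155: d = −4.5, limit −10.3, margin crossed.
- Equal missingness rates of 30% and 8% at the planned success rates lose 155 × 0.07 × 0.30 ≈ 3.3 Flebogrif failures and 155 × 0.05 × 0.30 ≈ 2.3 EVLA failures. Adding back 3 and 2, 142/155 vs 146/155: d = −2.6, limit −8.3, still non-inferior.

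**5. Why early failures must not be added back alone.** Suppose every missing failure is counted while missing successes stay excluded. With 10% of each missing and truth at 85% vs 95%, the mean difference becomes −10.9 and false non-inferiority falls to 1.8%. At 93% vs 95%, power falls from 80% to 75%. The remaining missing outcomes therefore need handling too.

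**The case against.** The rule is openly stated, and the sample size allows for the loss. ITT can be read mainly as analysis by allocated arm, and outcome-independent loss causes almost no bias. The second analysis already covers early failures that were re-treated at a participating centre. Details of imputation are commonly left to an analysis plan, which may exist. All of this stands and limits the size of the point. It does not remove it: the article goes beyond leaving missing outcomes open and fixes exclusion as the rule, and inflating the sample protects precision, not against bias.

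Three stronger readings are tempting and are not supported.
- A reader might infer that the rule favours Flebogrif. The documents do not say who is lost, and if failures return more readily than successes the rule is conservative.
- A reader might infer that documented failures will certainly be discarded. The article gives no count of early failures or of who drops out, so this may happen but is not known.
- A reader might infer that the planned result is fragile under equal missingness in both arms. The last case in step 4 shows that it is not. Crossing the margin there took 5 of 16 missing Flebogrif patients failing against 1 of 16 for EVLA, which is strongly arm-differential.

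Carrying an early failure forward also changes the outcome for those patients from status at 12 months to failure by 12 months. That is defensible, but it is a choice.

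**Conclusion.** The point holds in a limited form. The primary analysis labelled ITT is complete-case, contrary to the article's own ITT definition. Early failures without a recorded reintervention and without a 12-month scan are lost from both planned analyses. With more patients expected missing than failing, the result can turn on how they are handled.

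Under assumed rates equal in both arms, false non-inferiority at the margin ranges from below 3% to about 11%, against about 3% with full data. The upper figure requires failures to go missing nearly four times as often as successes. Should-fix, moderate confidence: the rule is certain from the text, while the size and direction of bias rest on assumptions that the document cannot settle.

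**What to change.** Replace the exclusion rule for the ITT analysis before the 12-month data are analysed:

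1. Score as failure any patient with no 12-month scan who had anatomical failure or a GSV reintervention documented before 12 months.
2. Impute the remaining missing outcomes by arm with a simple model using earlier duplex status. Seven surgeon terms should not be included, given roughly 7 to 10 failures per arm. This step keeps early successes in the analysis alongside early failures.
3. Add a tipping-point analysis that worsens the imputed Flebogrif success rate until the −10 margin is crossed, and report how extreme that is.
4. Keep the complete-case result as a sensitivity analysis.

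Cost: revised wording and a little programming, with no new data and no change in sample size. The interval may widen slightly. For patients under step 1 the outcome becomes failure by 12 months, which should be stated.

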#### Secondary outcome analysis

Categorical variables (technical success, safety, anatomical success, complications, clinical success, reinterventions, AASV reflux and neovascularisation) will be described as numbers with percentages. Between-group differences will be analysed using the χ^2^ test or the Fisher’s exact test where appropriate.

Continuous variables that are single measurements (operation time, intraprocedural and postprocedural pain scores) will be described as means with an SD in the case of normally distributed data and as medians with an IQR in the case of a non-normal distribution. Between-group differences will be analysed using the independent samples t-test or the Mann-Whitney U test depending on the data distribution.

Continuous variables that are measured at several moments (VCSS, CEAP Clinical score, aesthetic result and VEINES-QOL/Sym) will be described as means with an SD in the case of normally distributed data and as medians with an IQR in the case of a non-normal distribution. Between-group differences and change over time will be analysed using a linear mixed model. This type of analysis handles missing data well, making imputation unnecessary.

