#### Reinterventions

A reintervention is defined as a secondary treatment of the GSV in patients with anatomical failure after Flebogrif or EVLA treatment and assessed at 1 week, 1, 6, 12, 24 and 60 month(s) follow-up.

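### Reinterventions up to 60 months are compared as simple percentages although follow-up ends at withdrawal, so the late rates can be biased in a direction that depends on the denominator and on why patients leave

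*Protocol article*

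**What the plan says.** In the protocol article, the section on reinterventions gives this definition: "A reintervention is defined as a secondary treatment of the GSV in patients with anatomical failure after Flebogrif or EVLA treatment". The event is "assessed at 1 week, 1, 6, 12, 24 and 60 month(s) follow-up", so it accumulates over five years.

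The section on secondary outcome analysis names both the summary and the test. "Categorical variables (technical success, safety, anatomical success, complications, clinical success, reinterventions, AASV reflux and neovascularisation) will be described as numbers with percentages", and then: "Between-group differences will be analysed using the χ^2^ test or the Fisher’s exact test where appropriate".

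The section on withdrawal lets patients leave at any time and states: "If a patient is withdrawn from the study, follow-up ends".

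Two rules on missing data appear elsewhere, and neither reaches reinterventions. The primary outcome analysis says: "Patients with missing data on the primary outcome parameters will be excluded from analyses". The linear mixed model covers only the repeated continuous scores. The data analysis plan defines the intention-to-treat population as all randomised patients, but the article does not say whether that population, or those seen at a visit, is the denominator for the reintervention percentages.

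**The concern.** Reintervention is an event in time, observed for different lengths of time in different patients. A percentage with a chi-square test uses whether the event was seen and ignores how long the patient was observed. Anyone who leaves before 60 months without a reintervention must either be counted as event-free to the end or be removed, and the two choices move the estimate in opposite directions.

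The article lists five-year follow-up among the strengths of the study, and reintervention is one of the outcomes that shows whether the vein closure lasts. After 12 months only the 24- and 60-month visits remain, so there is room for attrition. The single loss allowance in the article, 10%, belongs to the sample size for the 12-month primary outcome. Patients know their treatment, so unequal withdrawal between arms is possible. In a trial meant to show that a new device is not worse, an analysis that can shrink a difference in durability deserves attention.

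**Working it through.** **The plan's own figures.** The article states no reintervention rate and no attrition at 24 or 60 months, so there is no figure of its own to reproduce on this point. The sample size (139 per arm, 278 evaluable; 155 per arm, 310 in total after 10% loss) does reproduce, but it concerns the 12-month primary outcome.

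**Assumed inputs (none from the article).** True 60-month reintervention risk F = 15% (Flebogrif) and 8% (EVLA). Withdrawal by 60 months d = 30% in each arm. Constant hazards, with withdrawal independent of reintervention.

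**Hazards per year.** Event: l = −ln(1 − F)/5. Withdrawal: m = −ln(1 − d)/5.
- Flebogrif l = −ln(0.85)/5 = 0.0325
- EVLA l = −ln(0.92)/5 = 0.0167
- m = −ln(0.70)/5 = 0.0713

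**Denominator A, all randomised.** Share with an event seen before withdrawal = l/(l + m) × [1 − exp(−5(l + m))].
- Flebogrif: 0.0325/0.1038 × (1 − 0.85 × 0.70) = 0.313 × 0.405 = 12.7%
- EVLA: 0.0167/0.0880 × (1 − 0.92 × 0.70) = 0.1895 × 0.356 = 6.7%
- Difference 5.9 points (from unrounded values), against a true 7.0

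**Denominator B, patients still followed at 60 months.** Under independent withdrawal this share equals F: 15.0% and 8.0%, difference 7.0. There is no bias.

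**Denominator C, still followed or event already seen.** Share = A/[A + (1 − F)(1 − d)].
- Flebogrif: 0.1268/(0.1268 + 0.595) = 17.6%
- EVLA: 0.0674/(0.0674 + 0.644) = 9.5%
- Difference 8.1 points

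**If withdrawal depends on the event.** Take denominator B and multiply the withdrawal hazard after a reintervention by a factor.

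| Factor | Flebogrif | EVLA | Difference (points) |
|---|---|---|---|
| 0.5 | 16.2% | 8.7% | 7.5 |
| 1 | 15.0% | 8.0% | 7.0 |
| 2 | 12.9% | 6.8% | 6.1 |
| 3 | 11.1% | 5.8% | 5.3 |

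Denominator B can therefore err either way.

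**Unequal withdrawal.** Assume true rates of 15% v 10% (difference 5.0). With withdrawal of 30% v 10%, denominators A, B and C give 3.2, 5.0 and 7.1 points. With 10% v 30% they give 5.8, 5.0 and 3.9.

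**Range and timing.** Over assumed 60-month risks of 5 to 20% and withdrawal of 10 to 30% by 60 months, the relative bias at 60 months is about −5% to −16% for A and about +5% to +19% for C. At 24 months on the same hazards it is only about 2 to 7% in either direction.

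**The case against.** The strongest reply is that this is largely a preference of method. The study ends five years after the last inclusion, so every patient has 60 months of potential follow-up and there is no staggered administrative censoring. A proportion at a fixed horizon is then a legitimate target, eroded only by withdrawal, loss or death. If withdrawal is equal between arms and unrelated to outcome, the chi-square test remains valid for the hypothesis of no difference. In the main example the all-randomised difference moves by 7.0 − 5.9 = 1.1 points, against a standard error of √(0.15 × 0.85/155 + 0.08 × 0.92/155) = 3.6 points. The denominator may also be fixed in a full protocol or analysis plan that is not shown.

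Much of this stands. It limits the size of the point, and silence on the denominator in an article is not itself a fault. What remains is that the article does name the summary and the test, and neither uses observation time.

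Three stronger readings are tempting and are not supported:
- **That the late rates are biased downward whatever the denominator.** Denominator B is unbiased under independent withdrawal, and denominator C is biased upward.
- **That a patient re-treated and later lost vanishes from the 60-month figure.** Nothing in the article says a recorded reintervention is discarded.
- **That not replacing withdrawn patients adds bias.** The rule, "After withdrawal, individual patients will not be replaced", costs precision and does not shift a rate.

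**Conclusion.** The point holds as a modest one. The stated analysis of reinterventions takes no account of unequal observation time, and the resulting bias, mainly at 60 months, has no fixed direction. With the article's own intention-to-treat population as denominator, the cumulative rate is understated whenever patients who leave early would later have been re-treated. Under the other two denominators it is right or overstated when withdrawal is independent of reintervention.

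With 15% v 8% and 30% withdrawal, one true difference of 7.0 points can be reported as 5.9, 7.0 or 8.1. These figures rest wholly on assumed rates, constant hazards and equal, independent withdrawal. The distortion at 24 months is small. Reintervention is a secondary outcome, and the 12-month non-inferiority conclusion is not affected.

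**What to change.** Record the date of each reintervention of the great saphenous vein. Analyse time from index treatment to first reintervention by Kaplan-Meier, or by cumulative incidence if death is to be treated as a competing event, with censoring at last contact. Report the rates at 12, 24 and 60 months with 95% confidence intervals and the between-arm difference, and compare arms with a log-rank test or a Cox model. Keep the counts and percentages as description, with the denominator stated.

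The cost is one date field, a change of analysis wording and slightly more analysis work. No visits or patients are added. Enrolment was still under way when the article was published, so the change can be made before the 60-month data exist. The method uses every observed event and all observed time, but it assumes that censoring is uninformative and does not remove bias from withdrawal related to prognosis. Reporting withdrawals by arm with reasons would let readers judge that.

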**Trial registration number:**

Overzicht van Medisch-wetenschappelijk Onderzoek in Nederland, NL-OMON25145, previously NL9527; Centrale Commissie Mensgebonden Onderzoek, NL74491.029.20.

STRENGTHS AND LIMITATIONS OF THIS STUDYThis study is a well-powered randomised controlled trial comparing mechanochemical ablation using Flebogrif with endovenous laser ablation in the treatment of great saphenous vein incompetence.The treatment will be blinded to outcome assessors during follow-up.Patients will be followed up for 5 years.The non-inferiority design does not allow for a superiority comparison.

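### Anatomical success at 1 week and 1, 6, 24 and 60 months is compared only by a test of difference, so a non-significant result could be misread as sustained non-inferiority

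*Protocol article*

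**What the plan says.** Primary outcome and Secondary outcomes define anatomical success in the same way at all visits: complete occlusion, or a recanalised segment of at most 5 cm. The non-primary visits are listed as follows: "Anatomical success (during other follow-up moments) is objectified at 1 week, 1, 6, 24 and 60 month(s) follow-up using DUS".

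The analysis differs by visit.

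- **12 months** (Primary outcome analysis): "The difference between the two groups will be presented as a percentage with a 95% CI". The decision rule is "If the lower limit of this CI does not exceed the non-inferiority margin of −10%, the intervention will be considered to be non-inferior". I read this as requiring the lower limit to lie above −10 points.
- **Other five visits** (Secondary outcome analysis): anatomical success is one of the variables in "Categorical variables (technical success, safety, anatomical success, complications, clinical success, reinterventions, AASV reflux and neovascularisation) will be described as numbers with percentages". The next sentence fixes the comparison: "Between-group differences will be analysed using the χ^2^ test or the Fisher’s exact test where appropriate". No interval or margin is given.

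The margin, "A non-inferiority margin of −10% is applied", is set in the sample size section for the 12-month hypothesis. The Introduction gives the aim as non-inferiority for anatomical success without naming a time point. The strengths and limitations box lists five years of follow-up, and adds: "The non-inferiority design does not allow for a superiority comparison".

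**The concern.** One endpoint is judged by two different kinds of inference. A test of the null hypothesis of no difference asks whether the data are incompatible with equality. A non-inferiority reading asks whether the data exclude a deficit of a given size. A large p-value answers neither question in Flebogrif's favour, because it may only reflect few patients or few events. A small p-value, in turn, may accompany an interval that excludes any deficit as large as the margin.

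At 24 and 60 months a reader of a non-inferiority trial will want to know how large a deficit is still compatible with the data. The planned output (numbers, percentages and a p-value) does not say. With fewer patients left, non-significance becomes more likely whatever the truth, so the possible misreading is most likely at the late visits.

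**Working it through.** **The plan's own figure.** Inputs from the sample size section: EVLA 95%, Flebogrif 93%, margin 10 points, one-sided 2.5%, power 80%.

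n per arm = (1.960 + 0.842)² × (0.95×0.05 + 0.93×0.07) / (0.10 − 0.02)² = 138.1, so 139 per arm and 278 in total, as stated. With 10% loss, 139/0.9 = 154.4, so 155 per arm and 310 in total, as stated. The sample size is sound for its purpose.

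**Method for the comparison.** For each scenario, all pairs of binomial counts were enumerated and two rules applied to each table:

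- Test of difference: z = d / √[2p̄(1−p̄)/n], two-sided 5% (uncorrected χ²), where d is Flebogrif minus EVLA and p̄ is the mean of the two observed proportions.
- Interval rule: d − 1.96 × √[p_F(1−p_F)/n + p_E(1−p_E)/n] > −0.10. The article names no CI method; Wald is assumed.

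The −10 benchmark is used at other visits only to compare the rules. The protocol sets it for 12 months alone.

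**Direction 1: non-significant, but non-inferiority not shown.** Assume 80% v 90%, a true deficit exactly at −10, with 108 per arm (about 70% of 155).

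- Test non-significant: 44.9% of trials.
- Test non-significant and lower limit at or below −10: 42.2%.
- Interval rule declares non-inferiority: 2.8%.

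Range over assumptions, always with a true 10-point deficit (share of trials non-significant; the interval rule declares non-inferiority in about 3% throughout):

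| Flebogrif v EVLA | 139 per arm | 93 per arm (60% of 155) |
|---|---|---|
| 85% v 95% | 19% | 35% |
| 80% v 90% | 34% | 52% |
| 75% v 85% | 45% | 60% |

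A single table shows the mechanism. Flebogrif 118/139 (84.9%) v EVLA 125/139 (89.9%) gives d = −5.0 points, χ² p = 0.21 and a 95% CI of −12.8 to +2.7. The p-value looks reassuring, but the interval does not exclude a 10-point deficit.

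**Direction 2: significant, but the whole interval lies above −10.** Assume 96% v 99% with 139 per arm.

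- Uncorrected χ² throughout: 26.5% of trials.
- Fisher's test whenever an expected count is below 5 (my reading of where it is appropriate): 14.0%. Expected failures here average 139 × (0.04 + 0.01)/2 ≈ 3.5 per arm, so this is the fairer figure.

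Example: 130/139 v 137/139 gives χ² p = 0.03 with a CI of −9.6 to −0.5. Expected failures are 5.5 per arm, so χ² would still apply under that reading; Fisher's test would give p = 0.06.

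**At the planning rates** (93% v 95%, 139 per arm) the difference test has 10.2% power. That is no defect, since the trial is not sized for it, but it means that a non-significant result says very little. There, 11.7% of trials are non-significant without meeting the interval rule, and 1.5% are significant with the interval wholly above −10.

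**The case against.** The strongest objection is that the protocol never draws the faulty conclusion. Its formal hypothesis, margin and decision rule are all tied to 12 months, and the other visits are openly secondary. A reader might infer that a non-significant p-value will be taken as proof of durable non-inferiority. No sentence says so, and the point should not be put that way. Nor does the article give sustained non-inferiority as the reason for five-year follow-up. This part of the objection stands.

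A reader might also see a flat contradiction between "The non-inferiority design does not allow for a superiority comparison" and the planned tests of difference. That is too strong. The remark is a general limitation of the design, and testing secondary outcomes for difference is not a superiority claim on the primary. The two fit together awkwardly, no more.

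It would also be tempting to apply −10 at every visit. The margin is justified only for 12 months, by reference to 85% success with Clarivein. In the 60-month scenario above it would accept 80%, below that reference, and five further formal non-inferiority readings would have no stated power or multiplicity provision. This stands too, and limits the fix.

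Finally, reporting detail is often left to an analysis plan, which is not shown here. But the protocol is not silent: it names the test for these visits, and that choice suits the trial's question poorly.

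**Conclusion.** The point holds in limited form. For the endpoint on which the trial seeks non-inferiority, the plan gives an interval at one visit and only a test of difference at the other five. That test cannot support a statement about sustained non-inferiority and could be misread as one. In the illustrative late-visit case the two rules are far apart (45% non-significant against about 3% declared non-inferior); the opposite conflict arises in 14% to 27% of trials at very high success rates, depending on the test used. These sizes rest on assumed long-term success rates and retention, Wald limits, and −10 as a yardstick outside the visit for which it was set. The qualitative conclusion does not depend on them. The 12-month primary conclusion and the 278/310 sample size are untouched.

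**What to change.** - For anatomical success at every visit, make the risk difference (Flebogrif minus EVLA) with a two-sided 95% CI the main result. Keep the χ² or Fisher p-value as supportive only.
- Handle reinterventions and missing data at these visits as in the primary analysis, so that the estimates are comparable over time.
- State that these intervals are descriptive. If a non-inferiority statement at 24 or 60 months is intended, prespecify and justify a margin for that visit before its data are examined.
- Optionally, soften the limitation on superiority: once non-inferiority is shown at 12 months, the same 95% CI may be read against 0 without spending further alpha.

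The cost is a few sentences of analysis wording and a little programming. No additional data or patients are needed.
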